**Methods:** This 6-month study will adopt a one-arm mixed method type 3 implementation-effectiveness hybrid design and be conducted in a single clinical site, the Chronic Viral Illness Service of the McGill University Health Centre. It will be guided by tools of implementation science (e.g., frameworks, outcomes). Five HIV physicians and 30 of their HIV patients will participate. The intervention will involve having patients complete the I-Score with an adapted version of the Opal smartphone app, prior to meeting with their physician. Both the patient and the physician will have access to the I-Score results, for consideration during the clinic visits at Time 1 (T1), T2 (3 months), T3 (6 months). The implementation strategy will focus on patient and provider involvement, education, and training, as well as on promoting the intervention's adaptability. The strategy's cornerstone will be the hiring of an Application Manager to facilitate implementation. Implementation, patient, and service outcomes will be collected (T1, T2, T3). The primary outcome of this pilot study is the intervention's acceptability (target: mean scale score of 4 on 5). Qualitative data obtained through provider focus groups (T2, T3), patient interviews (T2, T3) and the Application Manager's field notes (T1-3) will serve especially to evaluate the implementation strategy and inform any methodological adaptations.

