### *The I-Score intervention*

During the study, participating patients will visit with their HIV physician three times, at Time 1 (T1), month 3 (T2), and month 6 (T3), prior to which they will complete the I-Score, as instructed. This visit schedule was selected as it fits within guidelines for the clinical follow-up of HIV in Quebec (Ministère de la santé et des services sociaux, 2019), while maximizing the collection of repeated study measurements. Given COVID-19, one visit (T2) will be done remotely (by phone or teleconferencing), while the other visits will be held at the CVIS. The I-Score PROM contains 20 items, covering 6 domains of barriers to ART adherence. Respondents indicate how often each barrier made adherence difficult in the past 4 weeks, with a continuous scale, from never to always. [Additional details on measure scoring and interpretation will be provided to the REB as they become available]. For details on the measure's development see Engler et al., 2018, Engler et al., 2019, Lessard et al., 2019, Toupin et al., 2018.

The core intervention of this pilot consists of having individuals with HIV on ART register on the Opal app and complete the I-Score PROM prior to each of three consecutive visits with their HIV physician. The patients will receive a reminder to complete the I-Score one week before their visit and they will have immediate access to their results. The HIV physician will acquire the I-Score results before each visit via the ORMS dashboard, an appointment and questionnaire management tool integrated with Opal and designed specifically for healthcare providers. The option of graphically presenting scores over time will also be available, allowing physicians and patients to compare past and present scores. It is expected that patients and physicians will review the I-Score results so they can be considered during the clinic visit (see Figure 1).

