## Study metrics and instruments

Details on the constructs assessed; the instruments and metrics used; the chosen thresholds for success, if applicable; the participant group contributing data; and the timing of data collection are presented in Table 2. Many of the chosen metrics are based on those recommended by Stover et al. (2020). Importantly, the authors emphasize the need to standardize evaluation metrics in patient-reported measure implementation and to distinguish between those used to assess perceptions of the innovation and those used to assess the implementation strategy. Not meeting the set thresholds for success, in this study, will signify that modifications are necessary before proceeding to a definitive trial (Thabane et al., 2010).

Table 1. Schedule of study procedures for participants

| Procedure                                                  | Timeline               |                        |                        |                        |
|------------------------------------------------------------|------------------------|------------------------|------------------------|------------------------|
|                                                            | Prior to study start   | Study start (baseline) | Month 3                | Month 6                |
| Be screened and/or consent                                 | Patients
Physicians |                        |                        |                        |
| Attend educational meeting                                 | Physicians             |                        |                        |                        |
| Receive training on the I-Score measure and Opal           | Patients
Physicians | Patients
Physicians | Patients
Physicians | Patients
Physicians |
| Complete the I-Score measure via Opal                      |                        | Patients               | Patients               | Patients               |
| Examine the I-Score measure results via the ORMS dashboard |                        | Physicians             | Physicians             | Physicians             |
| Attend HIV patient-physician visit (online or in person)   |                        | Patients
Physicians | Patients
Physicians | Patients
Physicians |
| Complete the post-visit checklist                          |                        | Physicians             | Physicians             | Physicians             |

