### *Feasibility*

Feasibility relates to the extent to which our I-Score intervention is successfully used or carried out within the study site (Proctor et al., 2011). To determine feasibility, data will be collected on the Consent rate, defined as the proportion of approached eligible patients and physicians who consent to participate. Individuals who choose not to participate will be asked to provide select sociodemographic information (sex, year of birth, preferred language) and their reason(s) with a checklist on a refusal form (see the Appendix). If 70% or more agree to participate, the study will be judged feasible on this aspect. We will also examine the Retention rate, indicated by the proportion of patients and physicians who complete the study. Eighty percent will be considered the benchmark for success. Missing I-Score data rates due to network failure as well as patient and provider non-completion of self-reported questionnaire data will be calculated as well. The criterion for success on this metric is at least 90%. Furthermore, participants will complete the Feasibility of Intervention Measure (Weiner et al.,

2017), at T1, T2 and T3, a four-item self-report measure that is appropriate for different stakeholder groups (e.g., patients, providers). Example items include “This [evidence-based practice] seems possible” and “This [evidence-based practice] seems doable.” Average scores of at least 4, indicative of agreement on the 5-point response scale, will signify the I-Score intervention’s feasibility.

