### **Fidelity**

Fidelity is the degree to which the intervention was implemented as specified in the protocol (Proctor et al., 2011). It will be indicated by patient and provider adherence to core components of the intervention. Thresholds for success, from T1 to T3, are: 90% patient completion of the I-Score prior to meeting with the physician; 90% provider review of the patient’s I-Score results prior to or during the clinic visit.

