## **Data analysis**

### **Quantitative analysis**

Time 1 questionnaires for people living with HIV and for HIV physicians will be summarized with descriptive statistics. For continuous variables, the minimum, the maximum, the mean, and the standard deviation will be reported. For ordinal and nominal qualitative variables, we will report absolute and relative frequencies (proportions).

As, specified, for most quantitative metrics relating to Objectives 1 and 2, as recommended for pilot studies, score targets were set to evaluate the ability to proceed to a definitive trial (Thabane et al., 2010). For people living with HIV and HIV physicians, continuous outcomes expressed on a Likert scale will be summarized with the minimum, the maximum, the mean, and the standard deviation at T1, T2 and T3. Binary outcomes (yes or no) will be reported with absolute and relative frequencies (proportions) at T1, T2 and T3. The means and proportions of T1, T2 and T3 will be confronted with their corresponding thresholds for success, presented in Table 2. To study the tendency of means and proportions for people living with HIV over time, a Linear Mixed Model (LMM) or a

Generalized Linear Mixed Model (GLMM) will be used, for continuous and binary outcomes, respectively. The response variable of each model will be the corresponding outcome and the independent variable will be the time (T1, T2 and T3). The null hypothesis of no time effect on the corresponding outcome will be tested with a Student's t-test on the regression coefficient. If the null hypothesis is rejected, we will perform post-hoc Student's paired t-tests between all combinations of time points to show between which time points means and proportions differed significantly. Additionally, to verify if each threshold for success is met at the end of the study, we will test the null hypothesis that each mean or proportion at T3 is inferior to its corresponding threshold with a Student's t-test. For all analyses, a significance level of 5% will be adopted. Finally, where appropriate, Cronbach's alpha will be calculated to evaluate the internal consistency of subscales.

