| Objective 1
-Evaluate perceptions of the I-Score innovation                              | Acceptability             | Primary outcome:
Acceptability E-Scale (Tariman et al., 2011)                                     | Score
$M \geq 24$  | ✓                 | ✓          | T1, T2, T3 |
|                                                                                             |                           | % likely to recommend the I-Score (NHS, 2014)                                                               | $\geq 80\%$           | ✓                 | ✓          | T1, T2, T3 |
|                                                                                             |                           | Net Promoter Score (NHS, 2014)                                                                              | $> 0$                 | ✓                 | ✓          | T1, T2, T3 |
|                                                                                             | Appropriateness           | Perceived compatibility subscale (Moore and Benbasat, 1991)                                                 | Score
$M \geq 5.5$ | -                 | ✓          | T1, T2, T3 |
|                                                                                             |                           | Appropriateness of Intervention Measure (Weiner et al., 2017)                                               | Score
$M \geq 4$   | ✓                 | ✓          | T1, T2, T3 |
|                                                                                             | Feasibility               | Consent rate (and reasons for refusal)                                                                      | $\geq 70\%$           | ✓                 | ✓          | T1         |
|                                                                                             |                           | Retention rate                                                                                              | $\geq 80\%$           | ✓                 | ✓          | T1, T2, T3 |
|                                                                                             |                           | Missing PROM (I-Score) data rate (e.g., due to non-completion, network failure)                             | $\geq 90\%$           | ✓                 | ✓          | T1-T3      |

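### The feasibility criterion for missing data is reversed as written: success is set at 90% or more on a rate of missing data, and the text and Table 3 disagree on what is counted.

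*Protocol*

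**What the plan says.** The criterion appears in two places in the protocol.

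- **Objective 1, Feasibility.** The metric is introduced as "Missing I-Score data rates due to network failure as well as patient and provider non-completion of self-reported questionnaire data will be calculated as well". The next sentence sets the target: "The criterion for success on this metric is at least 90" per cent.
- **Table 3, Objective 1, Feasibility rows.** The row reads "Missing PROM (I-Score) data rate (e.g., due to non-completion, network failure"; its threshold is 90% or more, both the patient and physician columns are ticked, and the timing is T1-T3. (The text cites the metrics table as Table 2; its caption says Table 3.)

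Three other places bear on how the criterion is read.

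- **Fidelity** sets as success "90% patient completion of the I-Score prior to meeting with the physician".
- **Quantitative analysis** says of the end-of-study thresholds that "we will test the null hypothesis that each mean or proportion at T3 is inferior to its corresponding threshold".
- **Study metrics and instruments** attaches the consequence: "Not meeting the set thresholds for success, in this study, will signify that modifications are necessary before proceeding to a definitive trial".

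**The concern.** A high missing-data rate is a bad result, yet the threshold treats it as a good one. Neither place where the criterion is stated turns the metric into a completion rate, and because text and table agree, an isolated slip or a damaged table cell does not explain it. The figure is a pre-set progression criterion, so a literal reading reports the wrong result on this line: good data capture would signal a need for modification, and near-total loss would not.

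A second fault remains even after a reader silently flips the sign. The text counts I-Score loss through network failure together with questionnaires not completed by patients or physicians. Table 3 counts I-Score data only, but expects a physician figure. The protocol therefore does not settle which forms enter the rate, or whether one pooled rate or several must reach 90%. Settling either matter after the data are in would leave a choice that the pre-set threshold is meant to remove.

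**Working it through.** There is no sample-size or power calculation behind the 90% to reproduce; it is a fixed criterion. The check applies it as written and then as a completion rule.

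**Inputs**
- Sample (Summary): "Five HIV physicians and 30 of their HIV patients will participate".
- Administrations (The I-Score intervention): patients "complete the I-Score PROM prior to each of three consecutive visits with their HIV physician", so three per patient.
- Questionnaires (Table 1): patients and physicians each complete one at T1, T2 and T3.
- Who completes the I-Score (Table 1): patients only; physicians examine the results.

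**Expected forms, full planned sample**
- I-Scores: 30 × 3 = 90, or 30 per time point.
- Patient questionnaires: 30 × 3 = 90.
- Physician questionnaires: 5 × 3 = 15.
- All questionnaires: 90 + 15 = 105.

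**Step 1. What each rule requires**

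| Forms | As written: missing ≥ 90% | As completion ≥ 90% |
|---|---|---|
| 90 I-Scores | 0.90 × 90 = 81 or more missing, so 9 or fewer collected | 0.10 × 90 = 9 or fewer missing |
| 30 I-Scores at one time point | 27 or more missing | 3 or fewer missing |
| 15 physician questionnaires | 0.90 × 15 = 13.5, so 14 or more missing | 0.10 × 15 = 1.5, so 1 or fewer missing |

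**Step 2. Results at fixed missing rates.** At 0%, 5% and 10% missing, the rule as written is not met and the completion rule is met. At 50%, neither is met. At 90%, 95% and 100%, the rule as written is met and the completion rule is not.

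**Step 3. Chance of meeting the criterion.** Treat the 90 I-Scores as independent, for illustration only, since forms from one patient will be correlated. The count needed is 81 of 90: missing forms under the rule as written, completed forms under the completion rule. With a true missing rate of 5%, the probability is about 2 × 10⁻⁹⁴ as written and 0.985 as a completion rule. With 95% missing, the two values swap.

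**Step 4. Consistency with Fidelity.** That threshold needs at least 0.90 × 90 = 81 I-Scores completed before the visit. The feasibility criterion as written needs at least 81 missing. Since 81 + 81 = 162 exceeds 90, both cannot hold on the same forms, apart from forms that a patient completed and the system then lost.

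**Step 5. Consistency with the T3 test.** The planned null hypothesis places each proportion below its threshold, so rejecting it supports a value above the threshold. For a completion rate that is the right direction. For a missing rate with a 90% threshold, the test would look for evidence that more than 90% is missing.

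**Step 6. Does scope change the result?** Suppose 2 of 15 physician questionnaires and none of the 90 patient questionnaires are missing. Physician completion is 13/15 = 86.7%, which is under 90%. The pooled rate is 103/105 = 98.1%, which is over it. The same data pass or fail depending on a choice that the two places do not settle.

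**The case against.** The strongest reply is that this is a labelling error with an obvious intent. The criterion follows consent and retention benchmarks on which higher is better. The implementation strategy has the Application Manager oversee the completeness of the electronic measure in order to limit missing data. Fidelity asks for 90% completion, and the T3 test is set up for measures on which higher is better. An analyst would be very unlikely to report success with 81 of 90 I-Scores missing. This stands: a wrong decision from the sign alone is improbable. It does not make the stated criterion right, and it does not settle the scope.

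Three stronger readings are tempting, and the protocol does not support them.

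- *A study with complete data would fail, and one with almost no data would pass.* Only this row is reversed, out of eleven Objective 1 thresholds in Table 3. A study with 81 of 90 I-Scores missing through non-completion would still miss the patient fidelity threshold. The primary outcome, acceptability, has its own threshold and is not touched.
- *This is a go/no-go rule.* The protocol says that an unmet threshold means modifications are needed before a definitive trial. That is a progression criterion, not an automatic stop.
- *The physician cell in Table 3 can have no data.* That follows only from the table's narrow label. The Feasibility text includes provider questionnaires, which gives 15 expected forms, and the physician checklist records whether results arrived on time. The fault is a row label narrower than the text.

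The difference between the two definitions should not be overstated either. Both mention non-completion and network failure, and the table gives them only as examples. The substantive difference is whether study questionnaires count.

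**Conclusion.** The criterion is wrong as written in both places. On this one progression criterion, success needs at least 81 of 90 expected I-Scores missing, and complete data count as not meeting it, contrary to the 90% completion threshold under Fidelity. The intended rule is very probably completion of at least 90%, that is at most 9 of 90 missing. This is an inference from the Application Manager's role, the Fidelity threshold and the direction of the T3 test; the protocol does not state it. The mismatch in scope between text and table is a separate, smaller fault that survives correction of the sign.

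The counts assume all 30 patients and 5 physicians contribute at all three time points. The direction of the error does not depend on that assumption, nor on the independence used for the probabilities.

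**What to change.** Edit the Feasibility paragraph and the matching Table 3 row so that they say the same thing.

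1. Rename the metric as a completion rate with a threshold of at least 90%. Keeping a missing rate with a threshold of at most 10% is equivalent, but the T3 test would then have to be reversed for this row; the completion wording fits the test as it stands.
2. Align the scope: I-Score completion for patients only, and study questionnaire completion for patients and physicians. State whether the two groups are judged separately or pooled, since Step 6 shows that this can decide the result.

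How network failure is reported, and whether the table uses one row or two, is a matter of preference. An I-Score completion row will overlap with the fidelity row, which adds the requirement that completion precede the visit, so a few words distinguishing the two would help.

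The cost is one paragraph and one table row. Design, sample size and data collection do not change. The edit should be made before the thresholds are applied to any data.

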### *The implementation strategy*

The multilevel ePROM implementation strategy (Curran et al., 2012), designed for this study, addresses known facilitators and barriers to implementing ePROMs in routine clinical practice (Foster et al., 2018) and draws on recognized implementation strategies (Powell et al., 2012, 2015). Table 1 presents the correspondence between the facilitators and barriers targeted, the chosen implementation strategies to address them, and their relationship to components of the implementation framework used in this study, the CFIR. We will conduct an *Educational meeting* by teleconference with providers and other organizational stakeholders to formally teach them about the intervention and its rationale and respond to concerns. We will provide *Training and consultation* on the ePROM and app by hiring an *Application Manager* (AM). The AM will be available to patients and providers on an ongoing basis, as needed, preferentially by phone or teleconference. They will also help monitor the quality of PROM data. Appointing such a coordinator (or Quality Assurance officer) is a recommended strategy to minimize the impact of missing PROM data (Mercieca-Bebber et al., 2016). The AM will thus oversee the completeness of ePROM data collected and manage any system or software problems, which are potential disadvantages of computer or web-based PROM administration (ISOQOL, 2011). Hence, overall, they will facilitate PROM implementation. Another strategy aims to meaningfully *Involve patients and providers* in the I-Score's implementation. Individuals from both groups will provide input on the proposed study prior to its conduct. Following the I-Score administrations at T2 and T3, physicians will participate in a focus group (by teleconference), while a short semi-structured interview will be conducted with each patient (by telephone or teleconference). Throughout the study, the AM will take field notes on the problems encountered by participants and this feedback will enable *Cyclical small tests of change* to improve implementation, using an evaluation approach guided by the CFIR (Consolidated Framework for Implementation Research) (Keith et al., 2017). This way, we will *Promote adaptability* of the I-Score process, to enable adjustments to local considerations while maintaining the intervention's core components (i.e. I-Score completion by the patient via Opal prior to the clinic visit, review of scores by the physician in conjunction with the visit). Many peripheral components will be adaptable, such as the timing and number of reminders to complete the I-Score and how I-Score results are presented to providers on the ORMS dashboard.

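### The missing-data feasibility criterion points the wrong way in the Feasibility text and in Table 3: the metric is a rate of missing data, yet success is set at 90% or more

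*Protocol*

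**What the plan says.** The Feasibility section under Objective 1 introduces the metric as a count of losses: "Missing I-Score data rates due to network failure as well as patient and provider non-completion of self-reported questionnaire data will be calculated as well". The next sentence sets the target: "The criterion for success on this metric is at least 90" per cent.

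Table 3 carries the same pairing. The row label is "Missing PROM (I-Score) data rate (e.g., due to non-completion, network failure"), the threshold cell is 90% or more, and the timing is T1-T3.

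Three other places bear on how this should be read:

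- **Fidelity** (Objective 1) sets as success "90% patient completion of the I-Score prior to meeting with the physician".
- **Study metrics and instruments** gives the thresholds their force: "Not meeting the set thresholds for success, in this study, will signify that modifications are necessary before proceeding to a definitive trial".
- **Quantitative analysis** describes one test for all thresholds: "we will test the null hypothesis that each mean or proportion at T3 is inferior to its corresponding threshold with a Student's t-test".

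The section on the implementation strategy also makes the Application Manager responsible for the completeness of the ePROM data, and justifies the post in these words: "Appointing such a coordinator (or Quality Assurance officer) is a recommended strategy to minimize the impact of missing PROM data".

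**The concern.** Both parts of the metric, lost I-Score data and uncompleted questionnaires, are things the study wants few of. A floor of 90% on such a rate defines success as near-total loss. Text and table agree on the wrong direction, and nowhere is the metric redefined as completeness, so this is not a slip in one sentence that another part of the protocol corrects.

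The threshold also carries a decision. Because unmet thresholds mean changes before a definitive trial, the literal rule would send a study with almost complete data back for modification and would clear, on this item, one that had lost nearly everything. An analyst who notices the reversal would have to reinterpret a pre-specified criterion, perhaps after seeing the data, which is what fixing thresholds in advance is meant to avoid.

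**Working it through.** The 90% is a chosen criterion, not a derived figure, so there is nothing to reproduce. The check is to apply the rule as written and as completeness to the planned counts.

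**Inputs.** 30 patients (Summary; Setting and participants); three I-Score administrations each (The I-Score intervention); threshold 90% (Feasibility; Table 3). Expected I-Scores: 30 × 3 = 90.

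**Cut-offs.** 0.90 × 90 = 81 and 90 − 81 = 9. At a single time point, 0.90 × 30 = 27 and 30 − 27 = 3.

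| Missing rate m | As written (m ≥ 0.90) | As completeness (1 − m ≥ 0.90) |
|---|---|---|
| 0%, 5%, 10% | fail | pass |
| 20%, 50% | fail | fail |
| 90%, 95%, 100% | pass | fail |

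The two readings therefore give opposite verdicts at 10% missing or less and at 90% missing or more. Between those limits both fail.

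**Chance of passing.** Let X be the number missing among 90, binomial with true rate m. Independence across I-Scores and the values of m are assumptions made for illustration. As written, passing means X ≥ 81; as completeness, X ≤ 9.

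| True missing rate | P(X ≥ 81), as written | P(X ≤ 9), as completeness |
|---|---|---|
| 5% | about 2 × 10⁻⁹⁴ | 98.5% |
| 10% | about 3 × 10⁻⁷⁰ | 58.8% |
| 20% | about 2 × 10⁻⁴⁶ | 0.9% |
| 95% | 98.5% | about 2 × 10⁻⁹⁴ |

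**Conflict with Fidelity.** Pooled over the same 90 I-Scores, the completion target needs at least 81 completed before the visit, hence at most 9 missing. The feasibility criterion as written needs at least 81 missing. Provided a completed I-Score is not also counted as missing, both cannot be met.

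**The threshold test.** The null hypothesis is that the T3 value lies below its threshold. For this row as written, it says that less than 90% of data are missing, so rejecting it would be evidence of very high missingness. For a completeness rate, the same null says that completeness is below 90%, and rejecting it is evidence of success.

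**Denominator, needed for the repair.** Suppose a study exactly meets the 80% retention benchmark: 0.80 × 30 = 24 patients finish. If dropouts stay in the denominator:

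- I-Score completeness at T3 is at most 24/30 = 80%.
- Pooled, if all six leave before T2: at most (30 + 24 + 24)/90 = 78/90 = 86.7%.
- Pooled, if all six leave between T2 and T3: at most (30 + 30 + 24)/90 = 84/90 = 93.3%.

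A 90% completeness threshold on all enrolled patients could thus fail in a study that meets its retention target.

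**The case against.** The strongest reply is that the intent is plain. A success criterion of at least 90% can only sensibly mean completeness, the Fidelity target and the Application Manager's role say so, and no competent team would reward lost data. Acceptability, not this metric, is the primary outcome, and participant safety, data collection and the primary analysis are untouched. All of that stands, and it makes this an error of wording and direction, not a miscalculation. It does not remove the need for correction: the row is a pre-specified threshold with a stated consequence, and text and table both give the wrong direction.

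Three stronger readings are tempting, and the protocol does not support them.

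- A reader might infer that every plausible result gets the wrong verdict. It does not: rates above 10% and below 90% fail under either reading.
- A reader might infer that the threshold test under Quantitative analysis is itself wrong, or cannot be run on this metric. It is a general test suited to thresholds that are floors, and it can be run; it merely tests for the wrong thing if this row stays as it is. Whether it applies here is not certain either, since it concerns values at T3 and Table 3 gives this row the pooled timing T1-T3.
- A reader might infer that changing a word is enough. The metric also covers questionnaires (35 participants × 3 time points = 105 forms), which the count of 90 leaves out, and the retention arithmetic shows that the denominator matters.

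**Conclusion.** The point holds: the missing-data feasibility criterion is reversed in two places, the Feasibility text and Table 3. For I-Scores, the literal rule fails a study with at most 9 of 90 missing and passes one with at least 81 of 90 missing. The first is the result the study is aiming for, so the error matters in practice even though intermediate rates are unaffected. It contradicts the I-Score completion target under Fidelity and enters the decision on whether changes are needed before a definitive trial.

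The cut-offs rest only on the planned numbers and full enrolment. The pass probabilities also assume independent missingness and illustrative true rates; the conclusion does not depend on them.

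**What to change.** In the Feasibility section and in Table 3, rename the metric a data completeness rate, with a threshold of at least 90%, and:

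- **Report I-Scores and questionnaires separately.** The text combines them, while Table 3 names only the I-Score yet ticks physicians, who do not complete it.
- **State the denominator**, for example forms expected from participants still in the study at that visit, so that dropout is judged once, against the 80% retention benchmark, and the two thresholds do not conflict.

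With this wording the threshold test under Quantitative analysis needs no change. If the missing-data rate is kept instead, set the threshold at no more than 10% in both places and reverse the null hypothesis for this row, so that it states that the missing rate exceeds 10%.

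The cost is a sentence or two in the text and an edit to the Table 3 entry, split into two rows if I-Scores and questionnaires are listed separately. No new data and no change of design are needed. The change should be made before the thresholds are applied to data.
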